## Methods

### Design

This is a single-center, observer-blinded, randomized-controlled trial between parallel fast-track intervention and standard care groups with a qualitative substudy. We use the terms “fast track” and “standard care” (rather than “waitlist,” “delayed intervention,” or similar) as evidence suggests this term is preferred by patients (^9^).

Figure 1 illustrates the trial design. Referrals from health professionals are screened via telephone to ensure eligibility, followed by a baseline assessment. Eligible consenting participants are randomized to immediate intervention (fast-track) or eight weeks of standard care. Computer randomization is performed in permuted blocks, stratified by pulmonary rehabilitation completion in the last 12 months, and prepared by an investigator ([name]) not involved in the clinical administration of the trial. Allocation of participants is concealed in sequentially numbered, opaque, sealed envelopes, which are opened by nontrial research staff after participant details are recorded on the envelope. The results of randomization are communicated to administrative staff not involved in the trial who coordinate clinic bookings and assessments.

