**FIG. 1. f1:**
[figure not shown]
Randomized-controlled trial design.

Participants are assessed before randomization and again eight weeks later. The standard care group is then offered the intervention. As a consequence, there are no control group data available for comparison beyond the eight-week mark. Primary and secondary quantitative assessments are re-evaluated three monthly after clinic completion up to one year. Once participants have completed the intervention, they are contacted by telephone by an independent interviewer ([name]). Details regarding the qualitative substudy are outlined in the analysis section of this article below.

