### Standard care group

Before randomization, all participants will receive standard care comprising correction of inhaler technique, printed handouts specific to current inhaler(s), a COPD educational pamphlet (http://lungfoundation.com.au/wp-content/uploads/2015/12/COPD_FS-Sep2015.pdf), a written COPD exacerbation action plan, and a pedometer. Current smokers will receive advice on smoking cessation. Participants in the standard care group are encouraged to utilize health resources as usual.

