### Data collection

Outcome data are collected by research assistants not involved in delivering the intervention. Research staff involved in data collection are blinded. Primary and secondary outcomes are described in detail below. Table 3 describes the measures collected at various time points. In summary, data are collected at week 0 and 8 (face-to-face, in the patients' homes) to evaluate the quantitative outcomes. Patients allocated to the standard care group have data collected after completing the intervention (week 17). All participants have data collected at 3, 6, 9, and 12 months after completing the intervention by phone.

**Table 3. tb3:** Schedule of Enrollment, Interventions, and Assessments

Time point	Enrollment		Allocation	Postallocation																							Close out	
	−w 1	−w 2	0	W 1	W 2	W 3	W 4	W 5	W 6	W 7	W 8	W 9	W 10	W11	W 12	W 13	W14	W 15	W 16	W 17	W 22	W 30	W 35	W 43	W 48	W 56	W 61	W 69
Enrollment																												
Telephone screen	A																				F	S	F	S	F	S		
Informed consent		A																										
Standard care		A																										
Allocation			A																									
Intervention																												
Fast-track standard care				F	F	F	F	F	F	F	F	S	S	S	S	S	S	S	S									
				S	S	S	S	S	S	S	S																	
Assessment																												
Demographics		A																										
mMRC		A										A								S	F	S	F	S	F	S	F	S
CRQ		A										A								S							F	S
HADS		A										A								S	F	S	F	S	F	S	F	S
NRS		A										A								S	F	S	F	S	F	S	F	S
CAT		A										A								S	F	S	F	S	F	S	F	S
EQ-5D-5L		A										A								S							F	S
Height and weight		A										A								S							F	S
Step count				A								A								S								
Physical health check				F							F	S								S								
6MWT				F								S																
MNA				F								S																
EAT-10				F								S																
Hospitalizations		No. hosp. 1 year pre intervention																									No. hosp. 1 year post intervention	No. hosp. 1 year post intervention
Health care Utilization		A																									F	S

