### Data analysis

Descriptive statistics of demographic information and spirometry will be reported. We will analyze data by intention-to-treat according to the original allocated group. As exacerbations of COPD, which increase breathlessness, may occur during the trial and therefore affect our primary outcome, we will also perform a per-protocol analysis to only include participants who have not had an exacerbation during the eight-week fast-track intervention standard care period. We will analyze all normally distributed, continuous outcomes with an analysis of covariance, adjusting for participants' baseline values. For non-normally distributed outcomes, we will use Poisson or negative binomial regression models, as appropriate. The proportion of participants achieving the MCID for each outcome measure will also be compared using a chi-square test.

The primary analysis will be adjusted for pulmonary rehabilitation completion in the last 12 months as per our randomization plan. We will then undertake analyses to assess whether specific variables are related to the outcome in models including the study intervention, followed by multivariable analysis to assess which are independent predictors of the outcome. Factors likely to be important in this analysis include modified Medical Research Council at baseline, use of long-term oxygen, the presence of a caregiver in the home, FEV1 at baseline, and CRQ mastery score at baseline.

The variables that are measured over time (i.e., at the start, at completion of the intervention, 3, 6, 9, and 12 months postintervention completion) will be analyzed using a general linear model to account for the correlation within a subject. Due to the few time points, whether the effect of the intervention is sustained will be investigated by assessing the average difference between time point and the baseline value using a Tukey's test to maintain the overall error rate.

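### The durability analysis does not fix its reference by arm; on the default reading, the standard care arm's change from baseline includes its eight-week wait

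*Protocol article*

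**What the plan says.** The last paragraph of Data analysis covers the repeated measurements. It lists the time points as "at the start, at completion of the intervention, 3, 6, 9, and 12 months postintervention completion" and decides whether the effect persists by "assessing the average difference between time point and the baseline value", with Tukey's test to control the error rate.

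The Design section places baseline ahead of randomization: "Referrals from health professionals are screened via telephone to ensure eligibility, followed by a baseline assessment". The text under Figure 1 gives the sequence for the control arm: "Participants are assessed before randomization and again eight weeks later. The standard care group is then offered the intervention". Data collection confirms both assessments ("data are collected at week 0 and 8 (face-to-face, in the patients' homes) to evaluate the quantitative outcomes") and adds one more for the control arm: "Patients allocated to the standard care group have data collected after completing the intervention (week 17"). Everyone is then followed at 3, 6, 9 and 12 months after completing the intervention.

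The Discussion counts twelve-month durability among the study's assets. It also concedes that no valid comparator remains once the control period ends. It does not discuss which assessment serves as the reference for change.

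**The concern.** With no comparator after the control period, the quantitative evidence on durability is change within patients, so its meaning depends on the reference value. For a fast-track participant, the pre-randomization assessment is also the last one before the intervention. For a standard care participant it is not: eight weeks of usual care lie between that assessment and the intervention. If change is taken from the pre-randomization value, those eight weeks are counted as part of the intervention's effect, and the two arms' changes no longer measure the same thing.

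At stake is the size of the lasting benefit reported for the standard care arm, and for the whole sample if the arms are combined. An improvement during the wait would overstate the benefit; a decline would hide part of it.

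**Working it through.** **1. What baseline means in the article.** Design puts the baseline assessment before randomization. Intervention times the first fast-track clinic from it. Sample size is stated for change from baseline. The analysis of covariance in Data analysis adjusts for baseline values, which for the eight-week comparison must be pre-randomization values. No section defines a second baseline for standard care.

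**2. Listed time points against Table 3 (HADS, NRS and CAT).**

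| Label in Data analysis | Fast-track | Standard care |
|---|---|---|
| start (read as baseline) | -w 2 | -w 2 |
| no label | none | W 9 |
| completion | W 9 | W 17 |
| 3 months | W 22 | W 30 |
| 6 months | W 35 | W 43 |
| 9 months | W 48 | W 56 |
| 12 months | W 61 | W 69 |

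The six labels match the six fast-track assessments. Standard care has seven, so one has no label. With start read as baseline, the missing one is the end-of-control assessment (week 8 in the text, W 9 in Table 3). For the CRQ, Table 3 shows only completion and 12 months after the intervention, so only those two points are affected on that scale.

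**3. Splitting the standard care change.** For any post-intervention time t:

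(score at t - week 0) = (score at t - week 8) + (week 8 - week 0)

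Write w for the mean of the last bracket. It is change without the intervention, and it enters that arm's estimate in full at every t. At completion the interval is about 17 weeks, of which about 8 are waiting time.

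**4. Pooled estimate.** The document states no figure for this analysis. Its 56 per group reproduces: a two-sided t-test with difference 0.55, SD 1.0, alpha 0.05 and power read as 0.8 needs 53 per group, and 53/0.95 = 55.8, so 56. That figure is used here only as the weight: (56/112) × w = w/2, if the arms are pooled.

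**5. Size.** The documents do not give w. Over an assumed range, in CRQ units with a minimal clinically important difference (MCID) of 0.5 U:

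| w (assumed) | Standard care shift, share of MCID | Pooled shift | Pooled share of MCID |
|---|---|---|---|
| -0.25 | -50% | -0.125 | -25% |
| 0 | 0% | 0 | 0% |
| 0.10 | 20% | 0.05 | 10% |
| 0.25 | 50% | 0.125 | 25% |
| 0.50 | 100% | 0.25 | 50% |

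Taking the end-of-control value as the reference removes w from the standard care arm and leaves fast-track unchanged.

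**The case against.** The strongest reply is that the time points are anchored on the intervention, so the start may mean the start of the intervention. For standard care that would be the end-of-control assessment, and the problem would vanish. The wording allows this. But the stated contrast is with the baseline value, a term that the same section uses for the pre-randomization value, and on this reading it would be the pre-randomization assessment of standard care that had no label. Either way the reference has to be stated by arm. Nor is this merely a detail left to an analysis plan: the article names a reference and a list of time points, and the two do not fit the standard care schedule.

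Other parts of the reply stand and limit the point:

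- Pooling is not stated. The w/2 figure applies only if it is done.
- A reader might infer that the standard care package (inhaler technique, action plan, pedometer) contaminates only the standard care arm. It does not: "Before randomization, all participants will receive standard care comprising correction of inhaler technique", and Table 3 puts it in the same column as the baseline measures for everyone. Any effect that arises after measurement enters the fast-track change too.
- A reader might infer that the waiting-period data go unused. They are the comparator in the primary eight-week analysis.
- The direction of the bias is unknown. The decline mentioned in the Discussion concerns long-term follow-up and does not give w over eight weeks.

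**Conclusion.** The point holds as a correctable defect in a secondary, uncontrolled analysis. On the article's own use of baseline, the standard care arm's change at completion and later contains w in full, and a pooled change contains w/2 with equal arms. The conclusion rests on reading baseline as pre-randomization, which is the default but not explicit for this model. The sizes rest on assumed values of w.

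The documents do not support the stronger claim that the reference is wrong for half the participants: the wording is ambiguous, not explicitly fixed for both arms. Nor do they support any doubt about the primary result, because the randomized eight-week comparison properly uses the pre-randomization value in both arms. For the CRQ, Table 3 does not support a claim that every follow-up point is affected.

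**What to change.** In the last paragraph of Data analysis:

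- Define the reference for the durability analysis as the last assessment before the participant's own intervention: pre-randomization for fast-track, end of the control period for standard care.
- Include the end-of-control assessment as a time point for standard care.
- Report the post-intervention changes of the two arms separately before any pooling, and say whether they will be pooled.

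This changes wording only, because the assessment is already scheduled for all participants. There is one drawback to acknowledge. Any effect of the standard care package that arises after the baseline measurement would be removed from the standard care change but would remain in the fast-track change. That asymmetry is why the arms should be shown separately.

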### Cost-utility analysis

The primary outcome of the cost-utility analysis is the incremental cost per additional quality-adjusted life-year (QALY) at eight weeks, and the secondary outcome is the incremental cost per additional QALY at 12 months. Mean costs and effectiveness will be estimated from EQ-5D-5L; CRQ-Mastery scale; nonpharmacological interventions; outpatient visits; emergency department visits; hospitalizations; medication use; diagnostic and investigation use; and general practitioner visits. The mean incremental net monetary benefit will be estimated at potential threshold values for one additional quality-adjusted life year (^30^). Bootstrapping across 10,000 replicates will be conducted to robustly assess uncertainty for costs, effects, and cost-effectiveness, and cost-effectiveness acceptability curves will explore decision uncertainty (31, 32). Further sensitivity and scenario analyses will be undertaken to examine the effect of varying key parameter estimates on the outcome of the economic evaluation (^33^).

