## Abstract

***Background:*** Patients with chronic obstructive pulmonary disease (COPD) frequently experience breathlessness despite maximal medical therapy. Nonpharmacological management is effective in studies enrolling patients with a variety of respiratory diseases; however, the impact on patients with COPD is unclear.

***Methods:*** A protocol for a mixed-methods, single-center, observer-blinded, fast-track randomized-controlled, parallel-group trial comparing an immediate eight-week nonpharmacological Westmead Breathlessness Service (WBS) to a standard care control group is described.

***Population:*** At least moderate COPD (FEV1:FVC ≤0.7; FEV1%predicted ≤60%) and persistent disabling breathlessness (modified Medical Research Council ≥2).

***Intervention:*** Individualized prescription of nonpharmacological breathlessness interventions, including a handheld fan, breathing techniques, postures to relieve breathlessness, relaxation, nutritional advice, energy conservation, and exercise advice delivered by a team including doctors, nurses, a physiotherapist, an occupational therapist, a dietitian, and speech pathologist.

***Control:*** Participants who receive the WBS intervention after an eight-week period while receiving usual care (standard care group).

***Outcome:*** Primary outcome—Chronic Respiratory Questionnaire (CRQ) Mastery subscale. Secondary outcomes include numerical rating scale of breathlessness intensity, unpleasantness, and confidence managing breathlessness; quality of life as measured by other CRQ subscales; Hospital Anxiety and Depression Scale score; daily step count; health resource utilization 12 months pre- and postintervention; and cost-effectiveness. Qualitative analysis of participant interviews will provide additional context for interpreting the quantitative results.

***Discussion:*** This study aims to establish the efficacy and cost-effectiveness of an eight-week nonpharmacological breathlessness intervention in patients with COPD.

***Trial Registration:*** The Australian New Zealand Clinical Trial Registry ACTRN12617000499381 (06/04/17).

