### Cost-effectiveness data

We will evaluate health economic costs with an independent health economics researcher ([name]). The cost-effectiveness of adding the intervention to standard care for improving the HR-QoL will be investigated. Mean effectiveness and costs will be estimated from EuroQol-5 Dimensions-5 Levels (EQ-5D-5L) (HR-QoL); CRQ-Mastery subscale; nonpharmacological interventions (breathlessness pack as described above, action plan, clinic visits, home visits, telephone calls); outpatient visits; emergency department visits; hospitalizations; medication use; diagnostic and investigation use; and general practitioner visits.

Hospital and *Medicare Australia* data will be linked. Linked data from Centre for Health Record Linkage will be used to obtain health utilization data from the New South Wales (NSW) Admitted Patient Data Collection, NSW Emergency Department Data Collection, and NSW Ambulance Data. Inpatient stays will be costed using length of stay and case-mix weights for Australian Refined Diagnosis Related Groups (^28^). Outpatient clinic visits will be costed based on the Tier 2 Non-Admitted Care Services Classification (^29^) and emergency department visits using the urgency-related group cost weights (^29^). Medication and out-of-hospital services will be costed by *Medicare Australia* (https://www.humanservices.gov.au/customer/dhs/medicare). Costs associated with the intervention will be estimated as follows: hourly rates of local salaries plus on-costs for staff time; local reimbursement rates for travel costs; local hospital unit costs for the clinic; and the local hospital purchase price for equipment utilized for implementing the intervention (capital costs) and for consumables (handheld fan, telephone costs, pedometers, DVD, CD, patient handout folders).

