## Discussion

To our knowledge, this is the first RCT that evaluates the efficacy and cost-effectiveness of a multidisciplinary, integrated care, nonpharmacological breathlessness intervention for Australian patients with moderate to very severe COPD. There is evidence that nonpharmacological breathlessness clinics are helpful in the management of breathlessness in patients with a mixture of malignant and nonmalignant disease (5–8), but not specifically for patients with COPD. All previous trials have been undertaken in England (5–8), and there was a suggestion of differential efficacy between patients with malignancy and with nonmalignant conditions such as COPD (^6^).

The current study investigates the efficacy of a nonpharmacological multidisciplinary intervention in a more homogenous patient group than in previous studies. Our intervention is different; we have a larger multidisciplinary team and longer time frame. Strengths of the study include the use of robust primary and secondary outcome measures, use of a skilled MDT, and blinding of outcome assessments. The study uses handouts, CDs, and DVDs to help standardize the information that participants receive, while allowing for individualization of the intervention. The study is enhanced by the inclusion of qualitative data collection, economic evaluation of the intervention, and the durability of results over 12 months.

A limitation of this study is the inability to blind participants to group allocation, which may influence the study in terms of potential expectancy effects. In addition, this is a complex intervention, and thus, it is not possible to determine the individual impact of each element of the intervention, however, qualitative data may provide some insights. The relatively short intervention duration (eight weeks) may be too short to show change in some variables (e.g., weight). As standard care participants are offered the intervention after completion of the eight-week usual care period, there is no valid control group after this point. Interpretation of the long-term follow-up data may be difficult in the absence of a control group, given the decline in health over time, typical of COPD (^36^).

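### The 12-month incremental cost per QALY cannot be a randomized comparison with standard care, because the control arm is offered the service after week 8

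*Protocol article*

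**What the plan says.** The Cost-utility analysis section fixes two outcomes. For the first, "The primary outcome of the cost-utility analysis is the incremental cost per additional quality-adjusted life-year (QALY) at eight weeks". For the second, "the secondary outcome is the incremental cost per additional QALY at 12 months". The Cost-effectiveness data section gives the comparison that both serve: "The cost-effectiveness of adding the intervention to standard care for improving the HR-QoL will be investigated".

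The design limits how long that comparison lasts. Under Design, "Eligible consenting participants are randomized to immediate intervention (fast-track) or eight weeks of standard care". The text beneath Figure 1 continues: "The standard care group is then offered the intervention". It draws the consequence that "there are no control group data available for comparison beyond the eight-week mark", and the Discussion repeats that "there is no valid control group after this point". The Abstract also lists "health resource utilization 12 months pre- and postintervention; and cost-effectiveness" among the secondary outcomes.

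**The concern.** An incremental cost per QALY is a difference in mean cost divided by a difference in mean QALYs. For the question the article poses, both differences need participants who had standard care without the service over the whole horizon. The article says it has them only to week 8, yet names an increment at 12 months without qualifying it.

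The study is presented as establishing cost-effectiveness, and a one-year cost per QALY is a figure a funder may use. With no comparator attached to it, a two-treated-arms contrast or a before-after change could be taken for the effect of adding the service to usual care. The planned bootstrap of 10,000 replicates would describe sampling error around whichever number was computed. It cannot supply the missing comparator.

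**Working it through.** **Figures in the plan.** The article gives no economic figure to reproduce. Its one design calculation, 56 per group for CRQ Mastery, is not in question: the t-test calculation for a difference of 0.55 and SD 1.0 (two-sided 0.05, power read as 0.8) gives 52.9, and 52.9/0.95 = 55.7, so 56.

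**Timeline (Design, Data collection, Table 3).**
- The contrast of service with no service lasts 8 weeks: 8/52 = 15% of a year. For the other 44 weeks (85%) both arms have had the service or been offered it.
- Table 3 shows EQ-5D-5L at baseline, W9, W17 (standard care only), and W61 (fast-track) or W69 (standard care). No untreated utility is measured after W9.
- The final assessments are timed from the end of each arm's own intervention period: 61 − 9 = 52 and 69 − 17 = 52. Counted from allocation they are 8 weeks apart, and neither falls at week 52.

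**What the contrast by allocation recovers.** Assumptions, none from the article: utility gain *u* builds linearly over the 8 weeks of intervention and then holds; everyone in the standard care arm takes up the offer; there is no gain without the service. QALYs to week 52:
- Fast-track versus no service: (8*u*/2 + 44*u*)/52 = 48*u*/52
- Standard care arm versus no service: (8*u*/2 + 36*u*)/52 = 40*u*/52
- Difference between arms: 8*u*/52, and 8/48 = 17% of the first line

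| *u* | Fast-track vs no service | Between arms |
|---|---|---|
| 0.03 | 0.028 | 0.005 |
| 0.05 | 0.046 | 0.008 |
| 0.08 | 0.074 | 0.012 |

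The 17% does not depend on *u*. Carried to week 61, the first line becomes (4 + 53)*u*/52 = 57*u*/52 and the share 8/57 = 14%.

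**What happens to the ratio.** Let the service cost *c* per participant, let a fraction *p* of the standard care arm take it up, and leave downstream resource use aside. The incremental programme cost is (1 − *p*)*c*. The incremental QALYs are (48 − 40*p*)*u*/52 if the gain is sustained, and (4 − 4*p*)*u*/52 if it is lost once the intervention ends. At *p* = 1 the programme cost cancels in both cases. The QALY difference is then 8*u*/52 or zero. So both differences shrink, and the ratio can move in different ways depending on durability and uptake.

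**How much durability matters.** With *u* = 0.05 at week 8, the one-year gain against no service is:
- lost at week 8: 0.5 × 0.05 × 8/52 = 0.004
- linear decline to zero at week 52: 0.004 + 0.5 × 0.05 × 44/52 = 0.025
- sustained: 0.004 + 0.05 × 44/52 = 0.046

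The extremes differ by a factor of 48/4 = 12, whatever *u* is. These are chosen scenarios on a week-52 axis, not estimates.

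**Before versus after.** Twelve months pre against twelve months post has no control. It is open to regression to the mean and to the decline in COPD that the Discussion mentions. Excluding anyone hospitalized with an exacerbation in the preceding four weeks also shapes the pre-period, but only 4 of its 52 weeks.

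**The case against.** The best defence is that the article never says the 12-month increment is between randomized arms. Utilization is collected for a year before and after the intervention, and long-term outcomes are analysed against baseline, so a within-person increment would fit. The lack of a control after week 8 is disclosed twice. The 12-month result is only secondary, further scenario analyses are promised, and modelling detail normally belongs in a health-economic analysis plan that is not shown.

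Some of this stands. A reader might infer that no 12-month increment of any kind can be produced. The documents do not support that: immediate-versus-delayed, before-after and modelled figures can all be calculated. A reader might also infer that treating both arms drags the cost per QALY towards zero. That describes the two differences, not necessarily their ratio. Nor does any text say the figure will be presented as a randomized estimate. The later EQ-5D-5L assessments give some information on persistence, though uncontrolled. The absence of modelling detail is not itself a fault in an article.

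The rest does not cure the problem. The stated economic question is the service against standard care, neither economic section gives another comparator for 12 months, and the Discussion's caveat concerns long-term follow-up in general and is not applied to this outcome. The promised scenario analyses vary key parameters; they do not name an extrapolation.

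**Conclusion.** The point holds in this form: the secondary cost-utility outcome, read with the article's own economic question, is one that the design cannot estimate by randomized comparison. This is a contradiction in the text rather than omitted detail.

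By allocation, the 12-month contrast measures an eight-week head start. It recovers about 17% of the one-year QALY gain if the benefit is sustained and uptake is full, and none of it if the benefit ends with the intervention. The 12-fold spread shows how far a modelled one-year QALY gain depends on assumed durability. It does not measure the bias of either the delayed-start or the before-after comparison.

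The CRQ Mastery primary outcome, the sample size and the eight-week cost-utility result are untouched. Because this is a secondary outcome of the economic analysis, it should be fixed but is not critical.

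**What to change.** In the Cost-utility analysis section, state that the eight-week cost per QALY is the only within-trial randomized incremental result. Then relabel the 12-month result in one of these ways:
- preferably, as a model-based scenario analysis with explicit durability assumptions (effect lost, waning, sustained);
- or explicitly as a comparison of immediate with delayed start;
- or explicitly as an uncontrolled before-after comparison.

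Say whether 12 months runs from allocation or from the end of the intervention, since Table 3 uses the latter. Report the 12-month pre/post utilization as uncontrolled description, and carry the Discussion's caveat into the economic section.

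The cost is rewording and, for the first option, a small scenario model. No extra participants or visits are needed. The downside is the loss of a headline 12-month figure.
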